## 3 OBJECTIVES AND ENDPOINTS

| OBJECTIVES                                                                                                                                                                                                                                                                                                                                                                                                                                                                                                                                                                                                                                                                                                                               | ENDPOINTS                                                                                                                                                                                                                                                                                                                                                                                                                                      | JUSTIFICATION FOR ENDPOINTS                                                                                                                                                                                                                                                                                                                                        |
|------------------------------------------------------------------------------------------------------------------------------------------------------------------------------------------------------------------------------------------------------------------------------------------------------------------------------------------------------------------------------------------------------------------------------------------------------------------------------------------------------------------------------------------------------------------------------------------------------------------------------------------------------------------------------------------------------------------------------------------|------------------------------------------------------------------------------------------------------------------------------------------------------------------------------------------------------------------------------------------------------------------------------------------------------------------------------------------------------------------------------------------------------------------------------------------------|--------------------------------------------------------------------------------------------------------------------------------------------------------------------------------------------------------------------------------------------------------------------------------------------------------------------------------------------------------------------|
| Primary                                                                                                                                                                                                                                                                                                                                                                                                                                                                                                                                                                                                                                                                                                                           |                                                                                                                                                                                                                                                                                                                                                                                                                                                |                                                                                                                                                                                                                                                                                                                                                                    |
| 
The primary objectives of the study are as follows:
 
 
To evaluate the safety and tolerability of daily subcutaneous (SC) injections of vosoritide administered for 12 months in patients with selected genetic causes of short stature
 
To evaluate the change from baseline in age-sex standardized annualized growth velocity after 12 months of daily SC injections of vosoritide in patients with selected genetic causes of short stature
 
To evaluate the change from baseline in age-sex standardized height standard deviation score (SDS) after 12 months of daily SC injections of vosoritide in patients with selected genetic causes of short stature
 
 | 
The primary study endpoints include:
 
 
Incidence of adverse events per subject with particular attention to Grade 3 and 4 adverse events as well as to rates of hypotension
 
Change from baseline in age-sex standardized annualized growth velocity after 12 months of treatment
 
Change from baseline in age-sex standardized height SDS after 12 months of treatment
 
 | 
The rates of adverse events will describe the safety profile of vosoritide in this study population.
 
Change in annualized growth velocity and height SDS are standard measures of efficacy of growth promoting agents. They are highly correlated but as height velocity differs by age and gender, the height SDS takes these factors into account.
 |
| Secondary                                                                                                                                                                                                                                                                                                                                                                                                                                                                                                                                                                                                                                                                                                                         |                                                                                                                                                                                                                                                                                                                                                                                                                                                |                                                                                                                                                                                                                                                                                                                                                                    |
| 
The secondary objectives of the study are as follows:
 
 
To evaluate changes in body proportions from baseline after 12 months of daily SC injections of vosoritide
 
To evaluate changes from baseline in bone age/chronological age after 12 months of daily SC injections of vosoritide
 
                                                                                                                                                                                                                                                                                                                                                                                  | 
The secondary study endpoints include:
 
 
Change from baseline in seated height ratio after 12 months of treatment
 
Change from baseline in arm span minus standing height after 12 months of treatment
 
Change from baseline in bone age/chronological age after 12 months of treatment
 
                                                                                 | 
Seated height ratio and arm span minus standing height are standard measures of disproportionality. It is possible that vosoritide good affect axial versus appendicular growth in different ways and thus we want to assess its effect on proportionality.
                                                                                                 |

| OBJECTIVES                                                                                                                                                                                                                                                                                                                                                                                                                                                                                                                                                                                                                                                                            | ENDPOINTS                                                                                                                                                                                                                                                                                                                                                                                                                                                                                                                            | JUSTIFICATION FOR ENDPOINTS                                                                                                                                                                                                                                                                                                                                                                                                                                                                                                   |
|---------------------------------------------------------------------------------------------------------------------------------------------------------------------------------------------------------------------------------------------------------------------------------------------------------------------------------------------------------------------------------------------------------------------------------------------------------------------------------------------------------------------------------------------------------------------------------------------------------------------------------------------------------------------------------------|--------------------------------------------------------------------------------------------------------------------------------------------------------------------------------------------------------------------------------------------------------------------------------------------------------------------------------------------------------------------------------------------------------------------------------------------------------------------------------------------------------------------------------------|-------------------------------------------------------------------------------------------------------------------------------------------------------------------------------------------------------------------------------------------------------------------------------------------------------------------------------------------------------------------------------------------------------------------------------------------------------------------------------------------------------------------------------|
|                                                                                                                                                                                                                                                                                                                                                                                                                                                                                                                                                                                                                                                                                       |                                                                                                                                                                                                                                                                                                                                                                                                                                                                                                                                      | 
Bone age is used to predict remaining height potential. As vosoritide has the potential to advance bone age, the measurement of the ratio of bone age to chronological age is a standard way of evaluating if the growth promoting agent is leading to premature bone age advancement which may limit growth potential.
                                                                                                                                                                                                |
| Tertiary/Exploratory                                                                                                                                                                                                                                                                                                                                                                                                                                                                                                                                                                                                                                                                  |                                                                                                                                                                                                                                                                                                                                                                                                                                                                                                                                      |                                                                                                                                                                                                                                                                                                                                                                                                                                                                                                                               |
| 
The exploratory objectives of the study are as follows:
 
 
• To evaluate the pharmacokinetic (PK) profile of vosoritide in patients with selected genetic causes of short stature
 
• To evaluate changes from baseline in bone mineral density (BMD) after 12 months of daily SC injections of vosoritide
 
• To evaluate changes from baseline in vosoritide activity biomarkers and bone/collagen biomarkers after 12 months of daily SC injections of vosoritide
 
• To evaluate immunogenicity and assess impact on safety and efficacy measures after 12 months of daily SC injections of vosoritide
 
 | 
The exploratory study endpoints include:
 
 
• Standard PK parameters including Cmax, Tmax, half-life, etc...
 
• Change from baseline in total body BMD Z-score adjusted for height.
 
• Change from baseline in lumbar spine BMD Z-score adjusted for height.
 
• Change from baseline in cGMP and serum collagen X markers.
 
• Rates of vosoritide antibody development.
 
• Change from baseline in QoLISSY scale
 
 | 
We assume that this patient population will have similar PK parameters to those previously described in patients with achondroplasia but want to confirm that this assumption is correct.
 
As CNP affects bone growth parameters, we would like to explore the effects on bone mineral density as a safety measure.
 
cGMP and serum collagen X markers are pharmacodynamics measures of vosoritide efficacy. We want to explore the PK/PD relationship in this patient population and compare to that seen
 |

| OBJECTIVES                                                                                                                                                                                                                                                                | ENDPOINTS | JUSTIFICATION FOR ENDPOINTS                                                                                                                                                                               |
|---------------------------------------------------------------------------------------------------------------------------------------------------------------------------------------------------------------------------------------------------------------------------|-----------|-----------------------------------------------------------------------------------------------------------------------------------------------------------------------------------------------------------|
| 
 
To explore the relationship between genetic etiology and safety and efficacy
 
To evaluate changes from baseline in quality of life using the QoLISSY scale after 12 months of daily SC injections of vosoritide
 
 |           | 
in achondroplasia patients.
 
Vosoritide antibody assessment is a standard safety metric.
 
QoLISSY is a validated scale for quality of life measurement in children with short stature.
 |

During the extension study, all of the primary, secondary and exploratory aims and endpoints will remain the same, but the timeframe will be extended from 12 months until growth cessation or subject withdrawal from the study.

## 4 STUDY DESIGN

### 4.1 OVERALL DESIGN

We hypothesize that patients with selected genetic causes of short stature will benefit from treatment with vosoritide, a CNP analog which directly targets the growth plate. The selected genetic causes included in this study all have in vitro and in vivo evidence to suggest a prospect of benefit from vosoritide treatment.

This is a pediatric open-label, Phase I/II, single arm study of up to 75 subjects with selected genetic causes of short stature. This is a single site study being performed at Children's National Hospital. Subjects who are 3 to 10 years old inclusive for males and 9 years old inclusive for females who meet the clinical inclusion criteria defined below and meet all eligibility requirements will participate. After enrollment, subjects will be followed for a 6-month observation only period to establish a baseline height velocity, safety profile, and quality of life assessment. Vosoritide will then be administered daily via subcutaneous injection at a dose of 15 µg/kg/day for 12 months. Subjects with a positive response to therapy will be given the option to continue in the extension phase of the study during which they will continue to receive vosoritide until growth cessation.

### 4.2 SCIENTIFIC RATIONALE FOR STUDY DESIGN

In this study, we are focusing on six specific genetic subgroups causing short stature. These six groups all share a common final pathway of growth inhibition via increased activation of ERK1/2 signaling in the chondrocyte (the pathway targeted by vosoritide). These groups are also each relatively rare and within each group there is significant heterogeneity in the severity of short stature. Therefore, we think it is reasonable to combine the six groups into a single study cohort. To control for the interindividual variability, each subject will serve as his or her own control via the baseline 6 month observation only period. We propose to include up to 75 subjects in order to have at least 10 subjects in each subgroup. As the response to vosoritide therapy in this group is unknown, no formal power calculations are

planned. Rather, this is an exploratory study in a rare disease population, and we seek to obtain initial data which will influence future study planning. Additionally, at this time, it is not feasible to recruit a large enough cohort of any of the specific genetic causes to make this a meaningful study. It is difficult to predict the anticipated distribution of patients between each subgroup. In addition to the whole cohort analysis, exploratory analyses will be performed based on underlying genetic etiology. In the future, a randomized controlled study will be required in order to definitively prove efficacy. That is not the goal of the current study as this is a proof of principle study to assess whether subjects meeting these inclusion criteria have the potential to respond to vosoritide therapy.

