#### CNP deficiency due to mutations in the *NPPC* gene

To date, 2 families have been identified who have heterozygous mutations in the CNP gene itself (*NPPC*) presenting with dominantly inherited short stature with heights ranging from -4.3 to -2.3 SD. The affected patients were noted to have small hands as well but were otherwise healthy. Both mutations were missense variants (p.Arg117Gly and p. Gly119Cys) affecting highly conserved amino acids in the CNP ring. In vitro studies showed that these missense variants led to decreased cGMP production upon stimulation of the NPR-B receptor in both the homozygous and heterozygous state.

Patients with CNP deficiency in either the heterozygous or homozygous state are natural candidates for vosoritide as CNP replacement therapy. As further evidence to support this concept, Fujii et al. crossed a CNP knockout mouse model (*Nppc*-/-) with a mouse overexpressing a transgene for CNP. The *Nppc*-/- mice demonstrate decreased body length, bone size, and growth plate width. After crossing with the transgenic mice, all of these phenotypic features were greatly improved suggesting that circulating CNP is able to rescue the phenotype of global CNP deficiency.

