### 5.5 STRATEGIES FOR RECRUITMENT AND RETENTION

Research subjects will be directly recruited at Children's National Hospital and will be referred to the study by pediatric endocrinologists and geneticists throughout the United States. Direct recruitment at Children's National will occur when members of the endocrinology or genetics division identify patients who meet the inclusion criteria. The study will be publicized throughout the United States in a number

of ways. First, the study will be listed on national websites including [clinicaltrials.gov](https://clinicaltrials.gov) as well as the Pediatric Endocrine Society website. Second, an email will be sent to the pediatric endocrinology list serve describing the study and providing information about how to refer to the study. Third, [name] (the PI) will publicize the study during presentations at national meetings and when he speaks at other institutions. Additionally, study brochures will be handed out at the annual Pediatric Endocrine Society meeting. Fourth, [name] will send direct emails to pediatric endocrinologists and geneticists throughout the US informing them about the study and providing information about how to refer eligible patients. All subjects will be recruited from within the United States.

Once a subject has been referred by their pediatric endocrinologist, we will then arrange for a telephone call to review the study details and confirm that the patient meets the inclusion and exclusion criteria. Prior to the telephone call, a copy of the consent forms will be provided to the family. During the telephone call, we will review all study procedures and answer any questions from the subject and their guardian(s). If, after the telephone call, the subject and guardian are interested in enrolling in the study, we will make arrangements for the screening visit which will also serve as the start of the observation period.

As the inclusion criteria are quite straightforward, we anticipate a small number of screen failures and estimate that we will screen up to 100 subjects to enroll the cohort of up to 75 subjects.

To enhance study retention, a minimum of monthly phone calls are scheduled once the intervention begins. We anticipate that subjects enrolled in this study will be highly motivated to complete the study and do not anticipate a high dropout rate.

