### 9.2 SAMPLE SIZE DETERMINATION

This is an exploratory proof of principle Phase I/II study, and therefore, no formal sample size calculations were performed. The study size was chosen based on the feasibility of recruitment in this study time period.

Once the initial sample size of 35 subjects is achieved, we will discontinue recruitment of any genetic cohort with greater than 15 subjects. Additional recruitment efforts will then focus on achieving approximately 10 subjects in each of the cohorts.

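### Section 4.2 justifies up to 75 subjects by a minimum of 10 in each of six genetic subgroups, but the recruitment rule does not secure that minimum, and for NPPC it is unlikely

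*Protocol*

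**What the plan says.** Section 4.2 of the protocol says that "we are focusing on six specific genetic subgroups causing short stature", and then: "We propose to include up to 75 subjects in order to have at least 10 subjects in each subgroup". The same paragraph adds: "It is difficult to predict the anticipated distribution of patients between each subgroup". It describes the study as exploratory, without a power calculation.

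Section 9.2 gives a different basis for the size: "The study size was chosen based on the feasibility of recruitment in this study time period". Its recruitment rule is: "Once the initial sample size of 35 subjects is achieved, we will discontinue recruitment of any genetic cohort with greater than 15 subjects". It continues: "Additional recruitment efforts will then focus on achieving approximately 10 subjects in each of the cohorts".

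On NPPC, the CNP deficiency part of Section 2.2 states: "To date, 2 families have been identified who have heterozygous mutations in the CNP gene itself". Section 5.5 limits the recruitment area: "All subjects will be recruited from within the United States". It also expects up to 100 children to be screened. Section 5.1 requires pre-pubertal status, an age from 3 years to under 11 (boys) or under 10 (girls), and a height SDS of -2.25 or lower. Homozygous NPPC defects are eligible as well as heterozygous ones.

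Section 9.4.7 stratifies the analyses by genetic subgroup. Section 7.2 does not allow treated subjects who withdraw to be replaced.

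**The concern.** Sections 4.2 and 9.2 describe the same sample size with two different reasons (a subgroup minimum and feasibility) and two different targets (a floor of 10 and roughly 10). A floor in every subgroup also sits badly beside the statement that the distribution between subgroups is hard to foresee.

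A reader of Section 4.2 would expect six cohorts of at least 10. If one cohort ends with two or three children, the analysis by genetic cause says almost nothing about it, and a claim of proof of principle across all six causes would rest on fewer causes than the plan implies.

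**Working it through.** **Inputs.** Ceiling 75, six subgroups and a minimum of 10 each (Section 4.2). No cap before subject 35, closure of cohorts above 15 from then on, and a working target of about 10 (Section 9.2). Two known heterozygous NPPC families (Section 2.2). The protocol gives no expected share for any subgroup, so the shares in steps 3 and 4 are assumptions.

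**1. Is the total enough?** There is no power calculation to reproduce. The count is 6 × 10 = 60, which leaves 75 − 60 = 15 spare places. The total is sufficient.

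**2. Does the rule secure 10 in each cohort?**
- Five cohorts of 15: 5 × 15 = 75, leaving 0 for the sixth. None of the five exceeds 15, so the closing rule is never triggered. This holds whether the rule is applied once at subject 35 or continuously afterwards.
- Before subject 35 there is no cap. Five other cohorts need 5 × 10 = 50 places, so one cohort may hold at most 75 − 50 = 25. With 26, the places left are 75 − 26 = 49, and the target fails by arithmetic.
- In the extreme, all 35 in one cohort leaves (75 − 35)/5 = 8 for each of the others.
- A rule that did reserve 10 places for the last cohort would need 75 − 5 × cap ≥ 10, so a cap of 13 from the first subject (75 − 65 = 10; a cap of 14 leaves only 5), with all 75 places filled.

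**3. NPPC.** To expect 10 of 75, NPPC must supply 10/75 = 13.3% of enrolment. Binomial probability of at least 10 among 75 for assumed shares:

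| Assumed NPPC share | P(at least 10 of 75) |
|---|---|
| 1% | about 0 |
| 2% | 0.000003 |
| 5% | 0.004 |
| 10% | 0.21 |
| 13.3% | 0.55 |
| 16.7% (equal shares) | 0.82 |

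**4. All six cohorts together.** Enrolment was simulated with random arrivals, cohorts above 15 closed from subject 35 onwards, and 4,000 runs per case. There was no active steering towards small cohorts, and the five other cohorts shared the remainder equally.

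| Assumed NPPC share | P(all six reach 10), with the rule | Without the rule |
|---|---|---|
| 16.7% (equal shares) | 0.26 | 0.21 |
| 10% | 0.11 | 0.08 |
| 5% | 0.002 | 0.002 |
| 2% or 1% | 0 in 4,000 runs | 0 in 4,000 runs |

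The closing rule by itself changes little. Active recruitment into small cohorts after subject 35 would raise these probabilities wherever patients can be found.

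**5. What a small cohort costs.** The 95% half-width for a cohort mean change, in units of its standard deviation, is t(0.975, n − 1)/√n. It is 0.72 at n = 10, 1.24 at n = 5, 1.59 at n = 4, 2.48 at n = 3 and 8.98 at n = 2, and it is undefined at n = 1.

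**The case against.** The strongest reply is that Section 4.2 states an aim. It proposes a size with a purpose, admits in the same paragraph that the mix of patients is hard to predict, and calls the study exploratory. The operative text in Section 9.2 already says about 10 and directs later recruitment to the small cohorts. The efficacy and safety population in Section 9.3 is all treated subjects, and Section 4.2 labels the analyses by genetic cause exploratory.

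Much of that stands, and it rules out several stronger readings that a reader might infer:
- *That 10 per cohort is impossible.* It is not: 60 fits within 75, and the failure cases in step 2 are possible allocations that the document does not suggest are likely.
- *That the protocol promises 10 per cohort.* It states a purpose.
- *That subgroup size is the only reason given for 75.* Section 9.2 also gives feasibility, and having two reasons is part of what must be reconciled.
- *That all six cohorts are in doubt.* The evidence gap is specific to NPPC. Even there, two families is a count of known heterozygous cases and gives no prevalence. Homozygous children are also eligible, and the reported heights in Section 2.2 (−4.3 to −2.3 SD) all meet the height criterion.
- *That the main result is weakened.* The whole-cohort analysis does not depend on the split.

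What the reply does not remove is that a floor and an approximation are different targets, and that the stated floor is used to justify the size while no rule protects it.

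**Conclusion.** The point holds as a mismatch between a stated cohort size and a design that does not secure it. The inconsistency between Sections 4.2 and 9.2 is on the page, and the allocation arithmetic in steps 1 and 2 needs no assumption. That 10 NPPC subjects is unlikely is a judgement from two known heterozygous families combined with United States recruitment of pre-pubertal children in a narrow age range; the probabilities in steps 3 and 4 depend on assumed shares and on no active steering. Because treated withdrawals are not replaced, 10 enrolled could also mean fewer than 10 evaluable. The consequence is confined to the per-cohort results and what is claimed from them. It deserves correction, and the correction is small.

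**What to change.** In Section 4.2, replace the purpose clause that sets the floor of 10 with: *aiming for approximately 10 subjects in each subgroup where recruitment allows; this number is not assured and may not be reached for NPPC*. Use the same target and the same basis for the size in Section 9.2. Limit any per-cohort statement of proof of principle to cohorts that reach about that size. How very small cohorts are tabulated can be left to the SAP.

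The cost is a less favourable stated cohort size. No extra patients are needed, and the whole-cohort analysis is unchanged. A tighter cap (13 per cohort from the first subject, as worked above) would reserve places, but it could not supply NPPC patients who cannot be found, so the wording change is needed in either case.
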